### Statistical assumptions

The sample size of the studied group of patients was calculated using the online SWOG data calculator (Southwest Oncology Group). Based on the published data (in 2013) from our cancer center reporting the survival of patients with SCLC treated in our institution in 2003 to 2006, the expected number of patients was calculated. The 2-year survival was 36% for a group of 138 LD-SCLC treated in our institution [17]. We assumed that the 2-year survival in the studied group will be at least 50%. Taking α < 0.1 and a power of 0.80, the required sample size is 80 patients. Patients with diagnosed LD-SCLC, after radical treatment with remission or at least a good response after radical therapy, will be eligible for the study. Patients would have had radical radiotherapy to the chest with chemotherapy according to current international guidelines and institutional protocols. A detailed medical history will be collected regarding SCLC and comorbidities. During the qualification visit, the remission or good response should be confirmed based on chest/abdomen/pelvis CT examinations. After obtaining the patient’s informed consent to participate in the clinical trial, a brain MRI (MRI-1) will be performed and a baseline assessment of cognitive functions will be carried out using the battery of test listed below. Patients who at MRI-1 will be diagnosed with cerebral metastasis, depending on the size and number of lesions, will be eligible for WBRT (whole brain irradiation) or SRT (brain stereotactic radiotherapy). We propose SRT eligibility treatment criteria as in NSCLC according to the standards of the participating centers. All participating radiotherapy centers must have experience in SRT of brain metastases and up-to-date radiotherapy equipment suitable for SRT. Subjects who will not have cerebral metastases in the MRI-1 after chemoradiotherapy will have their next follow-up every 3 months (± 2 weeks) up to 2 years, and then every 6 months (± 2 weeks) up to 3 years. At the qualifying visit before MRI-1, and then every 6 months ±2 weeks), the patients will have a cognitive examination performed using dedicated neuropsychological tests and QoL assessment using the QLQ-C30 questionnaire. The tests will be conducted in the following order: California verbal learning test (CVLT) with a delay of 15 min, Color connection test (CCT), CVLT (after delay), Benton visual retention test (BNRT), verbal fluency test (VFT) by the certified psychologist (Table 2).

**Table 2 Tab2:** Schedule for observation of patients qualified for the study (24 months)

	initial visit	observation-months									
Months	−1	3	6	9	12	15	18	21	24	30	36
Patient consent	x										
Patient history and physical exam	x	x	x	x	x	x	x	x	x	x	x
Neurocognitive tests	x		x		x				x		
Quality of life	x				x				x		
Brain MRI scan and chest/abdomen CT scan	x	x	x	x	x	x	x	x	x	x	x

Overall survival will be measured using the Kaplan-Meier method from the date of the chest chemoradiotherapy start day until death, with preplanned subgroup analysis of brain metastases-free and brain metastases group. Assessment of clinical response by RECIST 1.1 criteria after brain SRT and WBRT in the brain will be determined. Comparison of neurocognitive tests scores in the subgroup with developed brain metastases before and after SRT and/or WBRT will be carried out using Student’s *t* test or in case of non-normal distribution by nonparametric tests. In the subgroup without developed brain metastases, the analysis of tests scores will be done in the same way. QoL scores and neurocognitive test scores will also be compared between subgroups with and without metastases to the brain with nonparametric tests. The tested differences will be considered significant if *p* value is less than 0.05. In order to consider important prognostic factors and stratification factors related to the disease and the treatment modality in the final analysis, initial tumor volume of intrathoracic disease (GTV), mode of chemoradiation treatment: concurrent vs sequential and bid (irradiation twice daily) vs oid (irradiation once daily) will be recorded in the data base.

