The aim of our study is to limit the irradiation of the brain to a group of patients who develop metastases to the brain. The primary end-point of the trial is the assessment of patients’ overall survival at 24 months after starting radical treatment with chemoradiotherapy. We assume that careful follow-up with regular MRI and the use of modern irradiation technologies in case of diagnosed early brain metastases will not worsen survival in LD-SCLC patients without PCI. The second primary endpoint is intracranial tumor control at 12 and 24 months after patient recruitment.

The secondary goals are (1) to assess the risk of developing brain metastases without PCI; (2) to assess the efficacy of radiotherapy of detected early brain metastases, including the feasibility and efficacy of SRT (stereotactic radiotherapy); (3) to monitor patients with neurocognitive tests and QoL questionnaires to asses and compare the influence of treatment on their performance and QoL in subgroups.

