## Methods/design

Patients diagnosed with LD-SCLC after completed radical treatment (chemoradiotherapy according to current international clinical guidelines) will be eligible for the study (Table 1). Eligible patients should have brain MRI at initial diagnosis with contrast before chemoradiotherapy and after completion of chemoradiotherapy. MRI studies will be acquired on a 1.5-T scanner using a dedicated coil for brain imaging using standard brain imaging MRI protocol: T1-, T2-, diffusion- weighted, and fluid-attenuated inversion recovery (FLAIR)], followed by T1-GD images.

**Table 1 Tab1:** Major eligibility criteria

Inclusion criteria	Exclusion criteria
Diagnosis of LD-SCLC	Lack of signed informed consent of the patient
A radical treatment (chemoradiotherapy according to current clinical guidelines) with remission or good/very good response to treatment	Disseminated neoplastic disease
Good general condition of the patient (ECOG/WHO − 0-2)	Contraindications for cerebral MRI examination
MRI of the brain in staging before chemoradiation treatment	The patient is not able to perform tests assessing cognitive functions
Signed informed consent	Poor performance status (ECOG/WHO > 2)

The eligibility criteria and doses for SRT: 1–3 asymptomatic or minimally symptomatic metastatic lesions up to 30 mm im longest diameter, with sum of volumes less than 15 ml (the largest lesion must have less then 30 mm in longest diameter and its volume should be less than 10 ml); SRT doses, specified at 80% isodose: 20 Gy for lesions with diameter equal or less than 20 mm, 18 Gy for 21–30 mm lesions.) PTV will be obtained by adding 2-mm margin to GTV.

Standard WBRT will pe performed for patients who do not qualify for SRT; 30 Gy in 10, 2-Gy fractions will be given in 2 weeks.

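### Overall survival is counted from the start of chemoradiotherapy, but patients enter only after completing it with a response, so 24-month survival is inflated relative to the 36% benchmark by an amount the article does not let us fix

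*Protocol article*

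**What the plan says.** The time origin of overall survival appears twice in the protocol article, and the two statements agree. The aims at the end of Background define the primary endpoint as "overall survival at 24 months after starting radical treatment with chemoradiotherapy". The analysis text after Table 2, under Statistical assumptions, says "Overall survival will be measured using the Kaplan-Meier method from the date of the chest chemoradiotherapy start day until death".

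Entry comes later. Methods/design opens with "Patients diagnosed with LD-SCLC after completed radical treatment". Statistical assumptions adds "Patients with diagnosed LD-SCLC, after radical treatment with remission or at least a good response after radical therapy, will be eligible for the study", and then "During the qualification visit, the remission or good response should be confirmed based on chest/abdomen/pelvis CT examinations". Consent, the first study MRI (MRI-1) and baseline testing follow.

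The benchmark is in the same section: "The 2-year survival was 36% for a group of 138 LD-SCLC treated in our institution". These patients were treated in 2003 to 2006. The article does not give the time origin of the 36%, and it does not say whether the cohort was limited to patients who completed treatment or responded. The design assumes at least 50% in the trial, with alpha below 0.1, power 0.80 and 80 patients. The article mentions no landmark and no delayed-entry method.

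**The concern.** A patient who dies during chemoradiotherapy, or before the qualification visit, can never be enrolled. Every enrolled patient therefore carries a stretch of follow-up, from time zero to entry, in which death is impossible. An ordinary Kaplan-Meier curve from chemoradiotherapy start stays at 100% over that stretch by design. A cohort of all treated patients loses people in the same period.

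The trial has one arm, so its primary result is read against the 36%. Guaranteed time raises the trial's figure and leaves the benchmark where it is. The trial could then appear to match or beat history even if survival without PCI is unchanged. That is the conclusion it sets out to support, and the abstract says that it may lead to less treatment. The abstract concedes bias from the lack of a randomised control arm. This bias is a separate one, and it can be reduced without a control arm.

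**Working it through.** **Inputs from the article.** Null 2-year survival 36%, alternative 50%, alpha 0.1 (sidedness not stated), power 0.80, N = 80.

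**Assumptions, none of them in the article.** A success rule, the interval t from chemoradiotherapy start to enrolment, and the share of comparable patients alive at entry.

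**1. Reproduce N = 80.** One-sample test of 0.36 against 0.50:
- Two-sided alpha 0.10 (one-sided 0.05): normal approximation 75, with continuity correction 82. The exact binomial first reaches 80% power at N = 81 (success at 37 or more alive, alpha 0.046, power 0.813).
- One-sided alpha 0.10: 55, 62 and 60 respectively, which does not match.

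The stated 80 is therefore consistent with two-sided 0.10. At N = 80 the matching rule is at least 37 alive, with P(X ≥ 37 | 0.36) = 0.038 and power 0.783. For one-sided 0.10 the rule is at least 35 alive, with type I error 0.093.

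**2. Survival given alive at entry, if nothing has really changed.** Let g be the proportion of comparable patients alive at the entry point. Then S(24 | alive at entry) = 0.36 / g, and the false-success probability is the binomial tail at N = 80.

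| g | 0.36 / g | P(X ≥ 37) | P(X ≥ 35) |
|---|---|---|---|
| 1.00 | 0.360 | 0.038 | 0.093 |
| 0.98 | 0.367 | 0.051 | 0.119 |
| 0.95 | 0.379 | 0.078 | 0.167 |
| 0.90 | 0.400 | 0.152 | 0.283 |

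**3. The same under a constant hazard.** λ = −ln(0.36) / 24 = 0.0426 per month, so g = exp(−λt) and S(24 | alive at t) = 0.36^((24 − t)/24).

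| t (months) | g | S(24 given alive at t) | P(X ≥ 37) | P(X ≥ 35) |
|---|---|---|---|---|
| 3 | 0.880 | 0.409 | 0.195 | 0.341 |
| 4 | 0.843 | 0.427 | 0.296 | 0.466 |
| 5 | 0.808 | 0.445 | 0.421 | 0.599 |
| 6 | 0.775 | 0.465 | 0.560 | 0.725 |

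These figures cover guaranteed time only. Selection of responders would add to them, and the article gives nothing from which to size it.

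**4. Consequence for power.** If the null is conditioned on being alive at entry, the 24-month horizon still runs from chemoradiotherapy start and the 50% target is kept, then exact power at N = 80 (one-sided 0.05) is:
- t = 3: null 40.9%, at least 41 alive needed, power 0.46
- t = 4: null 42.7%, at least 42 alive needed, power 0.37
- t = 6: null 46.5%, at least 46 alive needed, power 0.11

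If the alternative is shifted as well, at the same hazard ratio (ln 0.50 / ln 0.36 = 0.68), the required N is only about 82 to 91. The mismatched null is the problem, more than the sample size.

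**The case against.** The strongest objection is to the size. The interval from chemoradiotherapy start to enrolment is not stated. A constant hazard implies that 12% (t = 3) to 22.5% (t = 6) of historical patients had died by the entry point, and nothing in the article supports that. With 98% alive at entry the false-success probability is 0.051 against 0.038, a slight effect. The success rule is also inferred: the article states no cut-off, no sidedness and no explicit final test against 36%. All of this stands. A reader might take the 0.19 to 0.56 range as an established error rate, and the documents do not support that.

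Second, the source of the 36% is not at hand. If that cohort had already been limited to responders alive at a similar landmark, the mismatch would shrink. This also stands as a condition, although the article describes no such restriction. A shared origin at treatment start would not be enough, because early deaths would still be possible in one cohort and impossible in the other.

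Third, a reader might infer that the two primary endpoints contradict each other, since intracranial control is timed at 12 and 24 months from recruitment and survival is not. The article does not support that reading. They are different endpoints, each origin is stated, no planned analysis combines them, and counting intracranial control from recruitment is natural when MRI-1 follows consent.

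The unseen analysis plan is not an answer. The origin and the estimator are both stated in the article, so this is not a detail left for later.

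**Conclusion.** The point holds. The article fixes a time origin that precedes entry, admits only survivors with a response, and judges the result against a rate with no stated matching restriction. The direction of bias, towards concluding that omission of PCI does not worsen survival, is certain unless the benchmark cohort was already restricted in the same way.

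The size is not certain. Under the assumed rule of at least 37 of 80, the false-success probability runs from about 0.05 (98% alive at entry), through 0.08 to 0.15 (95% to 90%), to 0.19 to 0.56 (constant hazard, entry at 3 to 6 months), against 0.038 with no guaranteed time. Confidence is high for the direction only. A reader might also infer that changing the time origin alone cures the comparison. It does not, because the 36% would still describe a differently selected group.

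**What to change.** Choose one of two origins and state it in the aims and in the analysis text:
- count overall survival from enrolment (qualifying visit and MRI-1); or
- keep chemoradiotherapy start, with each patient joining the risk set at enrolment (delayed entry).

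In either case, replace the 36% with a historical rate from the same landmark: patients alive and responding after chemoradiotherapy, over the same horizon. Delayed entry without that step is not enough, because the resulting estimate is still conditional on survival to entry.

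If the 2003 to 2006 data cannot be re-cut, say that the comparison with 36% is biased upward. Report the enrolment-origin estimate with its confidence interval, and make no claim of success against 36%.

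This costs more than a change of wording. The primary endpoint's origin is amended in a trial that enrolled its first patient in September 2019. The benchmark must be re-extracted from the institution's own series, which needs patient-level dates and response data that the article does not show to exist. The null will also move. If the 24-month horizon still starts at chemoradiotherapy, the null rises. If it starts at enrolment, a constant hazard alone would leave it at 36%, and restriction to responders would be expected to raise it. The stated 80% power against 50% must therefore be restated.

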## Background

About 15% of patients with lung cancer are diagnosed with SCLC, one third of whom are patients with LD. According to the current standard clinical practice, patients with known LD-SCLC after a radical treatment (chemotherapy and chest radiotherapy) are eligible for prophylactic cranial irradiation (PCI) in case of a good response to treatment and lack of CNS dissemination. PCI aims to reduce the risk of brain metastases development and to improve survival, however, at the expense of possible losses of cognitive functions (attention, perception, memory, executive functions) because of brain irradiation.

This wide clinical acceptance of PCI is based mainly on the results of the meta-analysis published in 1999, which summarizes the observations of patients treated in the 70’s and 80’s [1]. At that time, the staging of the patient’s disease was mostly based on X-ray, biopsy and computed tomography (CT) scans were not performed. The treatment of patients was varied, and the methods (especially radiotherapy) differed significantly from those used nowadays. Three years after randomization, cerebral metastases occurred among 60% of patients in the non-PCI group, whereas only 40% of the patients in the PCI group were diagnosed with metastases to the brain. Based on the results of this meta-analysis, it has been demonstrated that there is a reduction in the risk of brain metastases by 20% after PCI, and an overall survival improvement of about 5% was observed. The patients analyzed in the meta analysis formed a heterogeneous group, which is difficult to compare with patients treated today mainly due to the phenomenon of stage migration. Certainly, in the prophylactically treated PCI cohort, there were some patients with already developed brain metastases.

In 2007, the results of a prospective study evaluating the influence of PCI on the survival and progression of the disease in the group of patients with disseminated small cell lung cancer were published [2]. Similarly, the irradiated group was compared with the group without PCI. It has been shown that after PCI treatment, there is a 2-time reduction in the risk of symptomatic metastases to the brain and an improvement in overall survival.

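### The preplanned survival split by brain-metastasis status starts the clock before the groups exist, so immortal time favours the metastasis group and can hide, shrink or reverse the harm of a metastasis

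*Protocol article*

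**What the plan says.** Under Statistical assumptions, in the text after Table 2, the protocol article fixes the estimator and the time origin: "Overall survival will be measured using the Kaplan-Meier method from the date of the chest chemoradiotherapy start day until death". The same sentence adds the split: "with preplanned subgroup analysis of brain metastases-free and brain metastases group".

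Three other statements show when patients can be classified:

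- Entry comes after treatment. Methods/design opens with "Patients diagnosed with LD-SCLC after completed radical treatment", so the survival clock is already running at enrolment.
- Some metastases are found at the first study scan ("Patients who at MRI-1 will be diagnosed with cerebral metastasis"). The article does not say whether these patients count in the metastasis group.
- All others are classified by later imaging: "Subjects who will not have cerebral metastases in the MRI-1 after chemoradiotherapy will have their next follow-up every 3 months", up to 2 years, then 6-monthly up to 3 years. Table 2 lists the same scan times.

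The text mentions no landmark, no time-dependent covariate and no restart of the clock at detection.

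**The concern.** The two curves start at a point when, for most patients, nobody knows which curve they belong to. Survival between chemoradiotherapy start and detection is credited to the metastasis group, although a patient who died in that interval could not have joined it. Those early deaths go to the metastasis-free group instead. The direction of this error is known in advance: it flatters the metastasis group.

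The trial has no control arm, and this is the only within-trial survival contrast by metastasis status that the article names. Readers will use it to judge whether a metastasis found on MRI and then irradiated shortens life. The bias pushes towards the answer that favours omitting PCI.

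**Working it through.** **The plan's own figure.** The sample size reproduces. With 36% against 50%, two-sided α 0.10 and power 0.80, using the variance at the alternative, n = (1.645 + 0.842)² × 0.50 × 0.50 / 0.14² ≈ 79. The exact binomial gives 81 and the continuity-corrected formula 82, against the stated 80. None of these uses the metastasis grouping.

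**Inputs for the bias**

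- 24-month survival of 50%, the planning target ("We assumed that the 2-year survival in the studied group will be at least 50" per cent). The historical figure is lower: "The 2-year survival was 36% for a group of 138 LD-SCLC treated in our institution".
- Metastasis risk at 36 months of 40% to 60%, an assumption. The upper end borrows the Background figure ("cerebral metastases occurred among 60% of patients in the non-PCI group"). That figure counts from randomisation in an older population and is not stated to be a risk in the absence of death. The lower end has no source in the article for patients without PCI.
- Constant hazards and follow-up to 36 months, also assumptions.

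**Model.** Let d be the monthly death hazard before metastasis, m = −ln(1 − risk)/36 the metastasis hazard, and θ the true hazard ratio for death after metastasis. Survival is S(t) = e^(−(d+m)t) + m/(d+m−θd) × [e^(−θdt) − e^(−(d+m)t)], and d is chosen so that S(24) = 0.50.

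**Worked case: θ = 1, risk 60%, per 100 patients**

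- d = ln2/24 = 0.0289; m = 0.916/36 = 0.0255; d + m = 0.0543; e^(−36 × 0.0543) = 0.141.
- Ever metastasis: 100 × (0.0255/0.0543) × (1 − 0.141) ≈ 40.2 patients.
- Deaths without metastasis: 100 × (0.0289/0.0543) × (1 − 0.141) ≈ 45.6. All deaths: 100 × (1 − e^(−36 × 0.0289)) ≈ 64.6. Deaths with metastasis: 64.6 − 45.6 = 19.0.
- All person-months: 64.6/0.0289 ≈ 2238. Person-months before any metastasis: 85.9/0.0543 ≈ 1580.
- Person-months of patients who never have a metastasis: 100 × {d[1 − 0.141 × (1 + 36 × 0.0543)]/(d+m)² + 36 × 0.141} ≈ 1078. The metastasis group is therefore credited with 2238 − 1078 = 1160, of which 1580 − 1078 = 502 come before detection.
- As planned: (19.0/1160)/(45.6/1078) = 0.0164/0.0423 ≈ 0.39.
- With the 502 months returned to the unaffected state: (19.0/658)/(45.6/1580) = 0.0289/0.0289 = 1.00.

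In this case 24-month survival appears as 72% with metastases and 35% without, although metastasis has no effect. At 40% risk the figures are 74% and 42%.

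**Same model, other true effects (apparent ratio)**

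| True HR | Risk 40% | Risk 60% |
|---|---|---|
| 1 | 0.44 | 0.39 |
| 2 | 0.76 | 0.68 |
| 3 | 1.01 | 0.92 |
| 4 | 1.23 | 1.13 |
| 5 | 1.40 | 1.32 |

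**Check with a more detailed simulation.** This assumed entry 0.5 year after treatment start, detection only at 3-monthly MRI, 3 years of follow-up and 50% of patients with an observed metastasis. True hazard ratios of 1, 2, 3, 4 and 5 appeared as 0.29, 0.53, 0.74, 0.93 and 1.09. A Cox model with time-dependent metastasis and delayed entry returned 1.00, 2.00, 3.00, 3.99 and 5.01. With 80 patients and a true ratio of 2, the ever/never ratio was below 1 in 99% of simulated trials and significantly below 1 in 71%.

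**Sensitivity to what the article leaves open**

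- 10% of patients with metastases at the first scan and front-loaded later ones (Weibull shape 0.7): true ratios of 1, 2 and 3 appear as 0.45, 0.83 and 1.18.
- 20% long-term survivors who never have a metastasis, 10% with metastases at the first scan, within-patient ratio 2: the fixed groups give 1.57, the time-dependent model 4.39.
- 30% long-term survivors with front-loaded metastases, within-patient ratio 2: 3.34 against 7.60.

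Across all scenarios the fixed-group ratio was about 0.22 to 0.45 of the time-dependent ratio.

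**The case against.** A reader might infer that the planned curves must come out the wrong way round. The documents do not support that. They give no hazard after metastasis, no timing of metastases and no share of long-term survivors. In the constant-hazard model, reversal stops at a true ratio of about 3 to 3.5. It stops earlier if metastases come early. It can vanish if a sizeable share of patients are metastasis-free long-term survivors, a group that the Abstract's Discussion expects. Only the statement that the bias can reverse the direction is supportable.

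A reader might also infer that the trial's main conclusion is compromised. It is not. The end of the Background names whole-cohort survival at 24 months and intracranial control as the primary endpoints, and its secondary goals do not include survival by metastasis status.

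The article names no survival test or hazard ratio between the two groups; its explicit comparisons concern neurocognitive and quality-of-life scores. The ratios above therefore measure the distortion and are not planned statistics. The objection has limited force, because two Kaplan-Meier curves split this way mislead without a p value.

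Finally, a condensed article may leave modelling detail to a fuller plan. That would answer a missing detail. Here the time origin, the estimator and the grouping are all stated, so a later plan would have to change the rule.

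Patients with metastases at the first study scan are classified at entry and add little or no differential immortal time. That reduces the bias but does not remove it.

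**Conclusion.** The point stands in a limited form. Followed as written, the subgroup analysis carries immortal-time bias in favour of the metastasis group. Under constant hazards, 50% survival at 24 months and 40-60% metastasis risk at 36 months, true hazard ratios of 1, 2, 3 and 4 appear as about 0.4, 0.7-0.8, 0.9-1.0 and 1.1-1.2. Moderate harm can look like benefit, harm near 3 largely disappears, and stronger harm is understated. These sizes rest on assumed hazards and timing; the direction of the immortal-time error does not. The grouping does not affect the primary whole-cohort estimate or the 80 patients.

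**What to change.** Replace the fixed-group Kaplan-Meier curves with a Cox or illness-death model in which brain metastasis is a time-dependent covariate that switches on at the detection MRI. Keep the time origin at chemoradiotherapy start, but let patients enter the risk set only at enrolment, because nobody can die in the study before then. State that patients with metastases at the first study scan are in the metastasis state from entry.

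For display, show landmark Kaplan-Meier curves by metastasis status at, for example, 6 and 12 months after enrolment, among patients still under follow-up. Note that landmarks dilute the effect: in the detailed simulation the 6-month landmark gave 1.60 for a true ratio of 2.00. Report survival from detection separately in the metastasis group. Present the time-dependent ratio as an association, since metastasis-free long-term survivors raise it above the within-patient effect.

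The cost is analysis wording and a somewhat less simple presentation. The scheduled MRIs already supply the detection dates, so no visits, data or patients are added.

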**Discussion:**

The results of this trial may contribute to changing of LD-SCLC clinical management by deescalating the treatment. There is a lack of prospective, recent studies in LD-SCLC patients with omission of PCI and modern radiation therapy technologies for developed brain metastases. The comprehensive neurocognitive function testing will help to assess the impact of modern radiotherapy (SRT) compared with WBRT and no-PCI in SCLC patients. A subgroup of long-term survivors, who will not develop brain metastases, will not be exposed to unnecessary brain irradiation with its deleterious consequences. The limitation of our study is a lack of parallel randomized control arm. This is a potential source of bias; however, randomized study will be difficult to complete for two major reasons: (1) limited population of LD-SCLC eligible for the study and (2) opinions of our patients, who after information and discussion about benefits and potential harms of PCI, often choose to omit PCI in our practice.

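### The planned before/after cognitive analysis pools SRT and WBRT, and no stated contrast supports the SRT-with-WBRT assessment that the Abstract announces

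*Protocol article*

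**What the plan says.** The Statistical assumptions section (text after Table 2) lists three cognitive contrasts.

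- In patients with brain metastases: "Comparison of neurocognitive tests scores in the subgroup with developed brain metastases before and after SRT and/or WBRT will be carried out", by Student's t test or a nonparametric alternative.
- In patients without: "In the subgroup without developed brain metastases, the analysis of tests scores will be done in the same way".
- Between the two: "QoL scores and neurocognitive test scores will also be compared between subgroups with and without metastases to the brain with nonparametric tests".

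The stated purpose goes further. The Abstract (Discussion paragraph) says: "The comprehensive neurocognitive function testing will help to assess the impact of modern radiotherapy (SRT) compared with WBRT and no-PCI in SCLC patients". The third secondary goal, at the end of the Background, is to assess and "compare the influence of treatment on their performance and QoL in subgroups"; those subgroups are not defined there.

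Modality is not randomised. Methods/design sets SRT criteria by number, size, volume and symptoms of the lesions, and then says: "Standard WBRT will pe performed for patients who do not qualify for SRT".

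**The concern.** SRT treats individual lesions; WBRT exposes the whole brain, which is also the exposure that PCI entails and that the trial wants to confine to patients who need it. A single before/after comparison over *SRT and/or WBRT* puts both into one number. It also takes in patients who receive both, whose change belongs to neither modality alone.

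At stake is how the cognitive results can be read. A pooled decline could be a large loss in a few WBRT patients or a modest loss in many, and the planned analysis could not tell these apart. A reader who expects the Abstract's SRT-with-WBRT assessment would find no analysis that provides it.

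**Working it through.** **1. Do the stated contrasts reach the stated aim?**

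| Contrast in Statistical assumptions | Groups | Separates SRT from WBRT? |
|---|---|---|
| Before/after, patients with metastases | one subgroup, SRT and/or WBRT | no |
| Before/after, patients without metastases | one subgroup, no brain metastases treated | not applicable |
| With versus without metastases | two subgroups by metastasis status | no |

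The factors to be recorded for the final analysis (intrathoracic tumour volume, concurrent or sequential treatment, once or twice daily irradiation) describe chest treatment. SRT and WBRT are named side by side for RECIST response and in the Abstract's efficacy endpoint, but those are tumour outcomes. No cognitive contrast separates the modalities.

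**2. What does the pooled change estimate?**

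With shares w and mean changes d for SRT only (S), WBRT only (W) and both (B):

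pooled change = w_S·d_S + w_W·d_W + w_B·d_B

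The documents give none of these values, so the following are assumptions. Take w_B = 0 and d_S = 0, so that pooled change = w_W·d_W.

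| Assumed d_W | WBRT share | Pooled change |
|---|---|---|
| -0.5 SD | 50% | -0.25 SD |
| -0.5 SD | 75% | -0.375 SD |
| -0.8 SD | 30% | -0.24 SD |
| -0.8 SD | 50% | -0.40 SD |
| -0.8 SD | 70% | -0.56 SD |

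The first and third rows almost coincide (-0.25 and -0.24 SD), although they assume different WBRT effects and different mixes. That is the identification problem in numbers. The effect sizes are assumed; the dependence on mix is algebra.

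**3. Could a formal SRT-versus-WBRT test be added instead?**

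The protocol gives no sample-size figure for cognition. Its 80 patients come from 2-year survival of 36% against 50% with power 0.80. Reading the 0.1 level as two-sided, (1.645 + 0.842)² × 0.25 / 0.14² = 78.9, so 79 patients; an exact binomial test first reaches 80% power at 81. The figure of 80 is therefore broadly reproduced, but it has no bearing on the cognitive analysis.

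For a two-group comparison of change scores I used the noncentral t distribution with noncentrality d·√(n1·n2/(n1 + n2)), n1 + n2 - 2 degrees of freedom, and level 0.05. The protocol does not say whether its 0.05 is one- or two-sided; I took two-sided. Inputs:

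- Patients with metastases: 30% to 60% of 80, that is 24 to 48. The 60% is the historical three-year rate without PCI in the Background; the 30% is assumed.
- SRT share 30% to 70%, and paired scores in 60% to 100% (both assumed).

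| Case | Group sizes | Difference detectable with 80% power | Power for 0.5 SD |
|---|---|---|---|
| Best: 48 patients, equal split, all evaluable | 24 and 24 | 0.83 SD | 40% |
| Worst: 24 × 0.6 = 14.4 evaluable, split 30/70 | about 4 and 10 | 1.75 SD | 12% |

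Adequate power for a moderate difference is out of reach across this range, before confounding is considered.

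**4. Is there always a test between SRT and a later WBRT?**

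No. Table 2 places cognitive tests at baseline and months 6, 12 and 24; the Abstract gives baseline, 12 and 24 months; the Statistical assumptions text gives every 6 months. Under Table 2, a patient given SRT at month 13 and WBRT at month 18 has no test in between.

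**The case against.** The best counter-argument is that *and/or* need not mean pooling: it could stand for a before/after test for each treatment received, with the split left to the full protocol or analysis plan of which this article is a condensation. That reading is possible. But two separate before/after tests are still not the SRT-with-WBRT assessment that the Abstract announces, so the mismatch between aim and analysis remains. It is also true that the Abstract promises only to help assess, and that a pooled change is a legitimate estimate of average change after brain irradiation under the surveillance strategy. It misleads only if read as an effect of one modality.

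Several stronger inferences are tempting, and the documents do not support them.

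- *That SRT and WBRT patients cannot overlap in disease extent.* Methods/design suggests this, but Statistical assumptions refers SRT eligibility to the standards of the participating centres. Selection may therefore vary between centres. Those two passages need reconciling; I take no view on which should stand. Confounding by indication remains either way.
- *That the case for omitting PCI rests on SRT sparing cognition.* The Abstract places the benefit mainly in long-term survivors who never develop metastases, and the Background makes survival and intracranial control the primary endpoints.
- *That the WBRT share can be put at 58%.* In the Background's CT/MRI comparison, MRI showed multiple metastases in 14% and a single one in 10%, so 14/(14 + 10) = 58%. That series compares detection, not outcomes of three-monthly surveillance, and patients with two or three lesions can qualify for SRT.
- *That splitting the analysis would yield an SRT-versus-WBRT effect.* It would not, given non-random allocation and the group sizes above.

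**Conclusion.** The point holds in a limited form. As worded, the plan has one before/after cognitive comparison over mixed brain irradiation and no contrast that separates the modalities, while the Abstract says the testing will help assess one compared with the other. The pooled figure cannot identify either effect. How far it departs from each depends on treatment mix and effect sizes that the documents do not give; -0.25 SD at 50% WBRT is an illustration resting on assumed changes of 0 and -0.5 SD.

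This is a mismatch between a secondary aim and its analysis. It is worth correcting before the data are analysed, but it does not touch the survival endpoint or the sample size.

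**What to change.** In Statistical assumptions, replace the single comparison with before/after change reported separately for three exposure classes: SRT only, WBRT only, and both. Give descriptive estimates with confidence intervals. Where no cognitive test falls between SRT and a later WBRT, keep the patient in the class for both and attribute the change to neither modality.

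Report the proportion of enrolled patients who ever receive WBRT; it bears directly on the stated aim of limiting brain irradiation.

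Restate the Abstract sentence so that it claims only a descriptive, non-causal view of SRT and WBRT, giving the reasons: modality follows disease extent, possibly with variation between centres, and the groups will be small.

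This changes analysis and wording only, not treatment, visits or sample size. It needs irradiation dates, which the article does not explicitly say are recorded but which any before/after analysis requires. The three statements of the cognitive test schedule should be reconciled at the same time, since they determine which tests count as before and after. The cost is smaller groups and wider intervals than the pooled test would show.
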